### Interventions

#### Control Treatment

The control group will only receive a care-as-usual approach. This includes a television mounted on the wall showing cartoons and the use of pharmaceutical treatment during the procedure such as the use of injected local anesthesia. In the event of noncooperation during the appointment, any retakes or rescheduling of appointments will be compiled by the resident dentist. One parent will be permitted to be present in the room during the procedure as part of the clinic’s usual protocol, and their presence will be recorded. Children allocated to the control group will be offered the possibility to try the VR game after the study period if they choose to do so.

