### Study Proceedings Including Data Collection

Participants will be identified by the resident dentist through the appointment scheduling system as requiring any dental procedure. Since DFA can arise from multiple different procedures such as simple cleaning to teeth extraction, dentists at the clinic will identify possible participants to include based on their cooperation, personality, and fears. An individual independent to the study will review consent with participants and parents. Written consent by the parents or legal guardian—including the child’s assent—will be obtained on arrival at the clinic the day of the procedure while completing the preprocedural questionnaire.

After verifying that the participant meets all the inclusion and exclusion criteria, the dental resident will log into REDCap only 10 minutes before the start of the intervention to minimize the risk of bias toward the intervention and to obtain the group allocation and announce it to the participant. Because of the nature of VR, no blinding of staff, participants, and parents or legal guardians will be possible. Baseline data collection prior to the dental procedure, including the sociodemographic questionnaire, recording of physiological parameters, and salivary alpha-amylase sampling, will take approximately 15 minutes to complete. The VR headset will be adjusted for the child’s size, and approximately 5 minutes will be allotted for children to familiarize themselves with the room, equipment, and game before the start of the procedure.

The intervention will last the entire time of the dental procedure, and the duration will be recorded for every patient. DFA assessment by proxy using the Venham Anxiety and Behavioral Rating Scale will be performed on site by the dental resident present and will also be filmed (if consent was given) to be evaluated by another member of the team at a later date.

As per the clinic’s protocol, if a child becomes restless and cooperation is impossible, the child will be held by his or her parents for the remaining duration of the procedure if it cannot be safely stopped at that time or if the procedure is considered an emergency. If the procedure can be safely stopped, rescheduling will be discussed with the parents including the possible need for sedation. The involvement of parents will be recorded as well as any other distractions used during treatment such as the use of stickers, teddy bears, or music.

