### Statistical Analysis

Analysis will be conducted using the SAS (SAS Institute) statistical analysis software (version 9.4). Descriptive statistics, by treatment, will be conducted for demographic and clinical variables and will be used to present sociodemographic and clinical data, parent and health care professional satisfaction levels, and procedural time. Due to a small sample size, we will also assess effect sizes.

For the pilot project, we plan to perform descriptive analyses of the sample as well as comparative analyses between the 2 groups. Nonparametric tests for procedural type, age, parental presence, parental and health care satisfaction levels, and baseline (T0) anxiety score measurement will be used to assess the composite outcome for mean salivary cortisol level and mean difference in anxiety score (using the Venham Clinical Cooperation Scale and Venham Clinical Anxiety Scale) between the experimental and control groups at T2. Analyses will be carried out according to the intention-to-treat principle, with a significance level (α) of .025, considering Bonferroni's correction.

For secondary outcome analyses, nonparametric tests adjusted for procedural type, age, and parental presence will be used to assess the mean procedural length at T2 using the VAS and 6-item tailored questionnaire, respectively. Comparison of dichotomous variables including the necessity for procedural retakes, use of other nonpharmacological interventions, and the occurrence of side effects will be assessed using the Cochran-Mantel-Haenszel test.

The study data will be recorded in the REDCap system belonging to URCA. The data manager associated with URCA and independent of the study will be responsible for the storage of the recorded data. However, a URCA biostatistician independent of the study will be responsible for the data analysis. The data analysis plan will be discussed with the principal investigator ([name]). Interjudge correlations will be conducted for the video tape analysis. Two judges will independently rate the anxiety measure on the videotapes. Subsequently, we will conduct intraclass correlation coefficient analyses to compare the scores for each of the recruited patients between the 2 judges.

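### Parental presence is a post-randomisation variable, so adjusting the VR-versus-TV tests for it can bias the contrast in either direction

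*Protocol article*

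**What the plan says.** The Statistical Analysis section of the protocol article states, for the secondary outcomes, that "nonparametric tests adjusted for procedural type, age, and parental presence will be used". Adjustment is explicit here, and procedural length is the outcome named.

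For the anxiety and biomarker comparison at T2 the wording is looser: "Nonparametric tests for procedural type, age, parental presence, parental and health care satisfaction levels, and baseline (T0) anxiety score measurement will be used". Presence is listed, but the sentence does not say that the tests are adjusted for it.

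Under Control Treatment, "One parent will be permitted to be present in the room during the procedure", and this presence is recorded. Experimental Treatment says the same in substance for the VR arm.

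Study Proceedings Including Data Collection gives the timing: "the dental resident will log into REDCap only 10 minutes before the start of the intervention", in part "to obtain the group allocation and announce it to the participant". The same section says that "no blinding of staff, participants, and parents or legal guardians will be possible". If cooperation becomes impossible and the procedure cannot be stopped safely, or is an emergency, "the child will be held by his or her parents for the remaining duration of the procedure". Parental involvement is to be recorded too, in wording separate from presence.

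**The concern.** A covariate in a randomised comparison should be fixed before allocation. Otherwise the adjusted contrast need not estimate the effect of assignment, which is what the intention-to-treat analysis promised in the same section is meant to give.

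Parental presence can be affected after allocation in two ways. First, a parent who knows the arm may choose to stay or leave because of it. Second, a parent who was outside may come in because the child cannot cooperate, and cooperation is something VR is meant to improve. Non-cooperation can plausibly also change how long the procedure takes, so the adjuster and the named outcome may share a cause that lies downstream of the arm.

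The pilot is meant to supply preliminary data for a larger trial. Its effect sizes and its analysis template may carry forward.

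**Working it through.** **Figures in the article.** Sample and Setting gives 20 children as 10% of 200: 0.10 × 200 = 20, or 10 per arm. This reproduces. The article gives no rate of parental presence, no rate of holding and no effect of presence on any outcome. The size therefore cannot be derived, only illustrated.

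**Order of events.** The arm is announced about 10 minutes before the start. The procedure follows, and presence is recorded during it. Holding, if it occurs, comes later still. The recorded value thus follows allocation, whenever the parent made up their mind.

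**Illustrative simulation (2,000,000 children per scenario).** All inputs are assumptions; only the 25% is anchored to the article, as the complement of the 75% completion expected under Primary Outcomes.

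- A = arm (0 TV, 1 VR); U = a standard normal distress factor.
- P0 = parent in the room from the start, with a probability that may differ by arm.
- C = child uncooperative: 25% with TV, 12.5% with VR, correlated 0.7 with U on the underlying scale.
- P = recorded presence: P0, or also C where the hold rule brings in an absent parent who is then counted as present.
- Outcome Y = −0.3·A + 1.0·C + 0.5·U + b·P0 + e, with e of SD 1. Effects are in units of that residual SD.

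The total effect is the difference in mean Y. The adjusted effect is the coefficient of A in a linear regression of Y on A and P. Hand check with equal initial presence: −0.3 + 1.0 × (0.125 − 0.25) = −0.425. With presence 70% TV, 50% VR and b = −0.3: −0.425 − 0.3 × (0.50 − 0.70) = −0.365. The simulated totals agree to within 0.004.

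| In room at start, TV / VR | Hold rule adds parents | b | Total | Adjusted | Change in size |
|---|---|---|---|---|---|
| 100% / 100% | yes | −0.3 | −0.426 | −0.426 | none |
| 50% / 50% | no | −0.3 | −0.424 | −0.424 | none |
| 90% / 90% | yes | −0.3 | −0.424 | −0.424 | 0.1% smaller |
| 70% / 70% | yes | −0.3 | −0.426 | −0.422 | 1% smaller |
| 50% / 50% | yes | −0.3 | −0.421 | −0.406 | 4% smaller |
| 50% / 50% | yes | −0.8 | −0.425 | −0.436 | 3% larger |
| 20% / 20% | yes | −0.3 | −0.423 | −0.356 | 16% smaller |
| 70% / 50% | no | −0.3 | −0.366 | −0.426 | 16% larger |
| 50% / 70% | no | −0.3 | −0.483 | −0.423 | 12% smaller |
| 70% / 50% | yes | −0.3 | −0.368 | −0.334 | 9% smaller |
| 70% / 50% | yes | +0.3 | −0.483 | −0.335 | 31% smaller |

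Where only the arm drives presence (the 70/50 and 50/70 rows without the hold rule), the adjusted value returns to about −0.425. That is the effect not passing through presence, a different quantity from the total effect of assignment.

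**No VR effect at all** (25% uncooperative in both arms, b = 0). With presence 70% TV and 50% VR plus the hold rule, adjustment creates a spurious +0.09. With 70/50 and no hold rule, the adjusted difference is zero. With presence 50% in both arms plus the hold rule (b = −0.3), it is −0.001. In these runs the spurious difference appeared only when both routes operated.

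**Against sampling error.** With 10 per arm the standard error of a difference is at least √(2/10) = 0.447 of the residual SD. The largest shift in the table is 0.483 − 0.335 = 0.148, and 0.148 / 0.447 = 0.33, so at most about a third of one standard error.

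**Sparse strata.** If a share p of parents is present in each arm, the chance that at least one arm has an empty presence stratum is 1 − (1 − a)², with a = p¹⁰ + (1 − p)¹⁰. For p = 0.9, a = 0.349 and the chance is 58%. It is 20% at p = 0.8 and 84% at p = 0.95.

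**The case against.** The strongest reply is that the article does not say when the parent decides. Every child is accompanied, parental presence is described as usual clinic practice, and a choice made on arrival fits the text. A reader might infer that presence is settled after the arm is announced; the documents do not establish that. What stands is that the recorded value is presence during the procedure, with the arm known, and nothing restricts the adjuster to a choice made beforehand.

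The holding route also needs steps that are not written down: the parent was outside, was brought in, and was then coded as present. Involvement is recorded in separate words, so holding may already be captured elsewhere. The rule is narrow too, since it applies only when the procedure cannot be stopped safely or is an emergency. The simulation brings in every absent parent of an uncooperative child when the rule is on, so it probably overstates this route. Still, nothing excludes a parent called in from counting as present.

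A reader might further infer that the adjustment removes part of the VR benefit. The documents do not support a direction: the change can be nil, towards no effect or away from it.

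Finally, explicit adjustment covers only the secondary outcomes, and the plan uses nonparametric tests whereas the simulation adjusts linearly. The figures therefore show possible direction and rough scale and do not predict the trial's result. The looser anxiety sentence also lists parent and professional satisfaction, which are measured at T2. That is a plainer case of the same kind, but a separate point.

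**Conclusion.** The concern holds in a limited form. The plan adjusts the secondary-outcome tests for a variable realised after open allocation, which the arm and the child's cooperation may affect. It also lists that variable, less clearly, for the T2 anxiety comparison. Adjusting for it can bias the VR-versus-TV contrast in either direction.

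The size is unknown. The range of 31% smaller to 16% larger rests entirely on assumed presence rates, cooperation rates and effects. There is no bias if presence is universal or unrelated to both arm and cooperation. In a pilot of 20 the shift is minor beside sampling error, and the practical difficulty of near-empty presence strata may be felt first. It deserves correction because it is systematic: a larger sample using the same analysis would narrow the interval without removing the bias.

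**What to change.** In the Statistical Analysis section, restrict adjusters to values fixed before allocation: age, planned procedure type and, where one is collected before allocation, the T0 value of the outcome. If parental presence is thought prognostic, add one question to the preprocedural questionnaire asking whether the parent intends to be in the room. Require that it be answered before REDCap is opened, and adjust for that answer only. The order should be stated, because baseline collection is given as about 15 minutes while allocation is opened 10 minutes before the start.

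Record actual presence from the start, being called in, and holding as three separate items. Report them descriptively by arm and do not use them as adjusters. No clinical rule needs to change.

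The cost is one questionnaire item, clearer coding of items that are largely recorded already, and a wording change. The small downside is that intended and actual presence will sometimes differ, so the adjuster will explain a little less variation than actual presence might. If nearly all parents intend to stay, it should be dropped as an adjuster, because with 10 per arm it would leave empty strata.

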### Ethical Considerations

Approval by the Ste-Justine Hospital research board of ethics (#2023-4985) was obtained in March 2023. An individual independent to the study will review consent with participants and parents. The information and consent form will be signed by one of the parents on the day of the visit. Upon enrollment, children are assigned codes used on all data collection forms to protect their confidentiality. Only the dental resident and the principal investigator will have access to the log that links the study codes to the participants. Patient-identifying information is kept separate from the case reports and is linked to study enrollment by a study ID number. The consent form also identifies all the information that may be collected during this study and details the use of videos that may be needed for further behavior evaluation using proxy scales with the possibility to opt out. All data collected by paper forms the day of the intervention will subsequently be transferred into REDCap. No recording of the child’s screen nor their game inputs will be collected. The intervention will be filmed and recorded, as the use of proxy scales will need further evaluation of the child’s behavior. As per usual, all information such as links between patient identifiers to study ID and paper copies of forms and questionnaires will be kept stored and double locked for 7 years (starting from the end of trial) at the principal investigator’s office at the research center.

## Results

This study will be conducted from May 2023 to May 2024, with results expected to be available in December 2024. The findings of the study will be disseminated through peer-reviewed publications.

## Discussion

The results of the study will allow us to gain insight on the feasibility and acceptability of the intervention and on the satisfaction of parents and health care professionals regarding the use of VR as a tool to reduce anxiety in pediatric dentistry, especially in children with SHCN. Due to the limited clinical studies about VR and pediatric SHCN populations in dentistry, this pilot study will guide potential future, larger, clinical trials.

### Challenges and Limitations

Individual experience with VR varies immensely, as some children may love to have an active distraction during dental treatment, while others may prefer to be present in the moment. As such, we acknowledge that the acceptance of VR use during dental treatment is a tool that may be useful for a certain population within a patient pool. Like all other distraction tools used in the dental setting, proper screening and patient selection are crucial during treatment planning. Moreover, the game design used during the study was created specifically for our study, so the results of our study may not be able to be extrapolated to a different setting with a different game design.

### Conclusion

The results of the study could be used to help us to better understand how VR distraction can reduce DFA in children with special needs and the acceptability of its use by parents, patients, and health care professionals during dental procedures. The results can be used as preliminary data for a future clinical trial on the use of VR in dentistry with special needs patients. In addition, this study will possibly allow for more comfortable and less traumatic dental care for pediatric patients. By exploring new avenues for behavior and anxiety management tools for pediatric dentistry, this study and its results will provide improved patient-centered care.

## Appendix

Multimedia Appendix 1 Study time points and data collection.

Multimedia Appendix 2 Parental satisfaction questionnaire.

Multimedia Appendix 3 Healthcare professional satisfaction questionnaire.

Multimedia Appendix 4 Venham anxiety and behavioral rating scale.

## Abbreviations

DFA: dental fear and anxiety
SHCN: special health care needs
URCA: Applied Clinical Research Unit
VAS: visual analog scale
VR: virtual reality
